#### Nonpenetrating sham acupuncture group

Patients of the sham group receive sham acupuncture under the tongue also during their next chemotherapy administration after study inclusion. Treated points will be 1 to 1.5 cun (a cun is defined as the width of the patient’s thumb at the knuckle) beside the verum acupuncture points Jinjin and Yuye using the dull side of the needle [26, 27].

#### Standard medical care group

Patients of the standard medical care group receive evidence-based dietary recommendations for dysgeusia [2, 12] during their first chemotherapy administration after study inclusion. Dietary advice will be provided by the study physician based on a self-help book of the German Cancer Society [28]. This self-help book was also given to the patients to take home.

### Data collection

Baseline data will be assessed before randomization (T_0_) and will include social demographics (age, sex, family status, education, employment), medical data of the patient (tumor type, staging, grading, relapse, menopausal status, chemotherapy type), and ratings for baseline outcome data.

### Primary outcome

The primary outcome is phantogeusia [11, 29, 30], a continuous abnormal taste sensation without an external oral stimulus, as assessed at follow-up (T_2_) by an 11-point NRS.

### Secondary outcomes

Secondary outcomes include phantogeusia, assessed between T_1_ and T_2_ using a daily patient log, as well as parageusia (abnormal taste of food), hypogeusia (reduced taste sensations), hypergeusia (increased taste sensations), xerostomia (dry mouth), stomatitis symptoms, appetite, and functional/social impairment, assessed at T_2_ and between T_1_ and T_2_ using a daily patient log with 11-point NRSs, respectively.

### Safety assessment

All adverse events will be recorded and assessed by the study physician at T_2_. According to good clinical practice guidelines, adverse events are defined as any untoward medical occurrence in the patient administered a medicinal product and that does not necessarily have a causal relationship with this treatment [31]. Thereby, serious adverse events are defined as any untoward medical occurrence that at any dose resulted in death, was life-threatening, required inpatient hospitalization, or resulted in persistent or significant disability/incapacity [31]. All participants will further be asked about any such event during the study period (between T_1_ and T_2_) and at follow-up (T_2_).

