## Methods/design

### Objectives

The aim of this study is to examine the efficacy and safety of hypoglossal acupuncture in the treatment of acute dysgeusia in patients with breast cancer undergoing chemotherapy.

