### Randomization

A researcher who was not involved in conducting the study generated a stratified (by age and type of chemotherapy because both variables are found to affect the course of dysgeusia [23, 24]) random allocation sequence with randomly varying block lengths using Random Allocation Software [25]. The randomization list is password-secured, and no person other than the aforementioned researcher is able to access it. On the basis of this list, the researcher prepared sealed and opaque envelopes sorted in ascending order of randomization. Allocation to the groups will be executed by the study physician, who is involved in neither the random sequence generation nor the assessment of study outcomes.

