### Blinding

First, patients of the two acupuncture groups will be blinded to whether they receive verum or sham acupuncture. Second, the outcome assessors delivering questionnaires to patients will remain blind to patients’ group allocations during the whole study period. Third, the statistician will be blinded to group allocation during data analysis by renaming groups with numbers.

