### Statistical analysis

Data will be analyzed using IBM SPSS Statistics for Windows software, release 22.0 (IBM Corp., Armonk, NY, USA). Patients’ characteristics will be presented separately for each group using descriptive statistics, including mean and standard deviation, median and range, frequencies and proportions, based on the data format and distribution.

Data analysis will be conducted according to the intention-to-treat principle; that is, all randomized patients regardless of compliance or withdrawal will be included. Missing values will be multiply imputed by the Markov chain Monte Carlo method [37, 38], yielding a total of 50 complete datasets. Statistical tests will be conducted in a hierarchical order, starting with the comparison of acupuncture vs. usual care, which in case of significant effects will be followed by the comparison of acupuncture vs. sham acupuncture.

The primary outcome will be analyzed as a function of the treatment group (verum acupuncture versus standard medical care), patients’ expectations, and their respective baseline values (linear covariates) using a univariate analysis of covariance. Between-group differences and 95% confidence intervals were estimated using two-sided *t* tests and an alpha level of 5%. If the analysis reveals a statistically significant between-group difference, a second univariate analysis of covariance on the primary outcome will be conducted as a function of the treatment group (verum acupuncture versus sham acupuncture), patients’ expectations, and their respective baseline values (linear covariates). Between-group differences and 95% confidence intervals were estimated using two-sided *t* tests and an alpha level of again 5%. Because of hierarchical testing of the hypotheses, no alpha level adjustment is necessary [39]. The same covariance models will be applied for secondary outcome measures; for those effect measures, confidence intervals and *P* values will be reported descriptively. Moreover, a Kaplan-Meier survival analysis will be used to analyze group differences regarding the time point of symptom relief based on the daily patient log. Data on tolerability and safety will be reported descriptively. No interim analysis will be conducted.

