## Discussion

Dysgeusia is often discussed as a less impairing, less significant side effect of chemotherapy. For patients, however, taste distortions during chemotherapy greatly affect appetite and quality of life, with few available effective treatment options [3, 6, 10]. Acupuncture as a relatively simple and short intervention that did not show severe side effects during the application of chemotherapy [17] and preliminary effects in patients with idiopathic dysgeusia [13] appears to be an important subject of research. The present trial was rigorously designed according to the CONSORT and STRICTA recommendations, including a nonpenetrating sham needling control, blinding of outcome assessors and patients, controlling of blinding success and expectation effects, and the use of standardized NRSs [22]. Particularly regarding the design of an ideal sham acupuncture control procedure, researchers broadly discussed how to mimic best the procedure of acupuncture and control for unspecific effects of expectation, conditioning, and therapeutic attention without provoking specific physiological effects [40–42]. It was argued that noninvasive sham acupuncture appears to be a more suitable control condition than the minimally invasive approach. In this study, using a noninvasive sham procedure should be feasible and blindable because participants do not have a visual control.

This trial should therefore generate the first evidence for the efficacy and effectiveness of hypoglossal acupuncture in patients with breast cancer who have acute chemotherapy-induced dysgeusia. Results can provide suitable information for further sham protocols and clinical acupuncture trials.

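### Adverse events are recorded and judged by the study physician, who allocates patients and so knows the arm; the safety comparison is therefore unblinded, and the Randomization section suggests otherwise

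*Protocol article*

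**What the plan says.** All references are to the protocol article.

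- **Objectives** sets a double aim: "The aim of this study is to examine the efficacy and safety of hypoglossal acupuncture" in acute dysgeusia during chemotherapy.
- **Randomization** states: "Allocation to the groups will be executed by the study physician, who is involved in neither the random sequence generation nor the assessment of study" (the quote stops one word short; the sentence is about outcome assessment). Allocation uses sealed, opaque envelopes prepared by a separate researcher.
- **Standard medical care group** states: "Dietary advice will be provided by the study physician based on a self-help book of the German Cancer Society".
- **Safety assessment** states: "All adverse events will be recorded and assessed by the study physician at T", with the subscript 2 following. It adds that participants will also be asked about events between T1 and T2 and at T2, without saying who asks.
- **Blinding** covers the patients in the two acupuncture groups, the statistician, and one group of staff: "the outcome assessors delivering questionnaires to patients will remain blind to patients’ group allocations during the whole study period".
- **Statistical analysis** states: "Data on tolerability and safety will be reported descriptively".
- **Discussion** lists among the design's strengths "blinding of outcome assessors and patients, controlling of blinding success and expectation effects", with no exception for safety.

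**The concern.** One role carries out the allocation, delivers one of the three interventions, and later decides what is written down as an adverse event and how it is classed. Knowing the arm can change how hard a physician probes for complaints, whether a minor local symptom is recorded at all, and how it is graded or attributed. Needling under the tongue would be expected to produce mainly minor, local and subjective events, and these leave the most room for such judgement.

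What is at stake is the safety half of the aim. The descriptive counts by arm are the trial's only evidence on harms. A reader who relies on the Randomization and Discussion sections would take the assessment to be separate from allocation and blinded, and for harms the document does not support that.

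**Working it through.** No formula settles this point. The check is to set the role assignments side by side.

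**1. Does the physician know the arm?** Randomization gives this role the execution of allocation from sealed envelopes. Acting on an envelope reveals its content. Independently of that, giving the dietary advice (Standard medical care group) identifies every patient in that arm. Two assumptions are needed: that *the study physician* is the same role throughout, and that executing allocation includes seeing the assigned group. The document uses one term in all three sections and names no second physician.

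**2. Does the physician assess harms?** Yes. Safety assessment gives this role both the recording and the assessment of every event at T2.

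**3. Is anyone blinded assigned to harms?** No section says so. The blinded assessors are described only as handing out questionnaires. The extra questioning of participants has no named asker, so it cannot be counted as blinded.

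**4. Do Randomization and Safety assessment contradict each other?** That depends on what *study outcomes* covers.
- Broad reading: safety is part of the aim, so adverse events are outcomes and the two sections conflict.
- Narrow reading: outcomes are only the NRS items. The abstract says all outcomes are rated on an NRS and mentions adverse events separately. The outcome sections do not list adverse events, and safety has its own heading. On this reading the sections are compatible.
- The narrow reading still leaves an overlap. Stomatitis symptoms and xerostomia are secondary outcomes, and a new or worse case of either also meets the broad adverse event definition in Safety assessment. The physician would then be judging symptoms that are named outcomes, although patients also rate them independently.

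On both readings the adverse event assessment is unblinded.

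**5. How sensitive is the comparison?** The planned size is 25 per arm, 75 in total (Sample size calculation). One patient more or fewer counted with an event moves that arm's rate by 1/25 = 4 percentage points. One error in each of two arms, in opposite directions, moves the difference by 2/25 = 8 points. This is the sensitivity of the counts. It does not estimate how many errors would occur, because the document gives no expected event rate.

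**The case against.** The strongest case on the other side has four parts.

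- **The document separates outcomes from adverse events.** This stands. The conflict between Randomization and Safety assessment is one reading and not a certainty, and the Blinding section promises nothing about adverse events.
- **Safety is only described, and physician assessment of events is ordinary practice.** It stands that no confirmatory test is at risk. It does not remove the problem, because descriptive counts by arm are still read as a comparison, and medical judgement of an event does not require the same unblinded person to elicit it.
- **Stomatitis and dry mouth are rated by the patients themselves**, at T2 and in the daily log. This stands for those symptoms and limits the damage. It does not cover other local events, such as pain or bleeding.
- **Asking blinded assessors about harms could unblind them**, since patients may mention needling or dietary advice. This is a fair cost. It is limited if the NRS questionnaire is completed first.

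A reader might go further and infer that the physician's contact at T2 exposes the verum/sham blind or biases the primary rating. The document does not support this. It is silent on the order of procedures at T2, which a condensed article may leave to the full protocol. The primary outcome is the patient's own NRS rating on a questionnaire delivered by blinded assessors, and the success of the verum/sham blinding is to be checked with the Bang index. Nor can a relative risk for the bias be given, since any such figure would only restate assumed miscounts.

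**Conclusion.** The point holds for safety only. Adverse events are elicited and judged by a role that knows the arm, so the between-arm description of harms is open to ascertainment and classification bias for all 75 planned patients. The direction and size of that bias cannot be derived from the document. The Randomization statement about outcome assessment is misleading on the narrow meaning of *outcomes* and contradicted on the broad one. The primary and secondary NRS outcomes are not shown to be affected. The conclusion rests on the two assumptions in the first step of the check: one study physician role throughout, and allocation carried out with sight of the assigned group.

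**What to change.** 1. At T2, have the existing blinded outcome assessors collect adverse events with one standard scripted question, identical in all three arms, **after** the NRS questionnaire has been completed.
2. Have the study physician judge seriousness and causality from that record.
3. Reconcile Randomization with Safety assessment. Either state that *study outcomes* means the NRS outcomes and that the study physician has a role in safety, or reword the separation so that it is true for harms as well. Qualify the blinding claim in the Discussion accordingly.
4. State in the report that adverse events already collected by the physician were assessed unblinded. Recruitment began in January 2015 and was still open when the article was published, so the new procedure helps only patients still to be assessed. For the others, disclosure is the remedy.

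The cost is a short extra form, a fixed order at T2 and a wording amendment, with no added staff. The downside is a small risk that a patient's answer reveals the arm to the assessor, limited by taking the NRS first. Patients given dietary advice know their treatment in any case, so the gain is clearest for verum against sham.

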### Treatment expectancy and credibility

Treatment expectancy and credibility will be assessed by the Treatment Credibility Scale [32, 33] and the Bang blinding index [34, 35] to examine possible confounding effects due to expectation and conditioning and to control the success of the blinding toward the verum and sham acupuncture. Expectancy will be assessed at baseline (T_0_), and credibility will be assessed directly after the acupuncture treatment (T_1_) and at follow-up (T_2_).

### Sample size calculation

No study has yet investigated the effect of hypoglossal acupuncture for chemotherapy-induced dysgeusia; as such, a sample size estimation on the basis of previous effect sizes was not possible. Therefore, a sample size of *n* = 25 patients per group was considered sufficient to detect an effect of *d* = 0.8, using a two-sided *t* test between independent groups (verum acupuncture versus standard medical care) with an α of 0.05 and a power of 1 − β = 0.8, as calculated using G*Power software (release 3.1.3; Kiel University, Kiel, Germany) [36].

### Statistical analysis

Data will be analyzed using IBM SPSS Statistics for Windows software, release 22.0 (IBM Corp., Armonk, NY, USA). Patients’ characteristics will be presented separately for each group using descriptive statistics, including mean and standard deviation, median and range, frequencies and proportions, based on the data format and distribution.

Data analysis will be conducted according to the intention-to-treat principle; that is, all randomized patients regardless of compliance or withdrawal will be included. Missing values will be multiply imputed by the Markov chain Monte Carlo method [37, 38], yielding a total of 50 complete datasets. Statistical tests will be conducted in a hierarchical order, starting with the comparison of acupuncture vs. usual care, which in case of significant effects will be followed by the comparison of acupuncture vs. sham acupuncture.

The primary outcome will be analyzed as a function of the treatment group (verum acupuncture versus standard medical care), patients’ expectations, and their respective baseline values (linear covariates) using a univariate analysis of covariance. Between-group differences and 95% confidence intervals were estimated using two-sided *t* tests and an alpha level of 5%. If the analysis reveals a statistically significant between-group difference, a second univariate analysis of covariance on the primary outcome will be conducted as a function of the treatment group (verum acupuncture versus sham acupuncture), patients’ expectations, and their respective baseline values (linear covariates). Between-group differences and 95% confidence intervals were estimated using two-sided *t* tests and an alpha level of again 5%. Because of hierarchical testing of the hypotheses, no alpha level adjustment is necessary [39]. The same covariance models will be applied for secondary outcome measures; for those effect measures, confidence intervals and *P* values will be reported descriptively. Moreover, a Kaplan-Meier survival analysis will be used to analyze group differences regarding the time point of symptom relief based on the daily patient log. Data on tolerability and safety will be reported descriptively. No interim analysis will be conducted.

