**Methods/design:**

The study is a randomized controlled trial comparing a single verum acupuncture treatment with two active comparators: sham acupuncture and dietary recommendations. Sample size calculation revealed a total of 75 patients pending an alpha of 0.05, a power of 0.8, and an estimated effect size of 0.80. Patients with breast cancer undergoing platinum- or taxane-based chemotherapy will be included if they present with phantogeusia (abnormal taste sensations without an external oral stimulus) with an intensity of 4 points or above on an 11-point numeric rating scale (NRS). The primary outcome is phantogeusia; secondary outcomes include parageusia (abnormal taste of food), hypogeusia (reduced taste sensations), hypergeusia (increased taste sensations), xerostomia (dry mouth), stomatitis, appetite, and functional impairment. All outcomes will be assessed at baseline and prior to the next chemotherapy administration using an 11-point NRS for each. All adverse events will be recorded.

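### The two stratification factors, age and type of chemotherapy, are left out of every ANCOVA, so intervals and tests are conservative to the extent that these factors predict outcome beyond baseline and expectation

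*Protocol article*

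**What the plan says.** **Allocation.** The Randomization section stratifies "by age and type of chemotherapy because both variables are found to affect the course of dysgeusia". Within strata it uses a "random allocation sequence with randomly varying block lengths using Random Allocation Software". Block lengths, the age cut-point and the number of chemotherapy categories are not given.

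**Primary model.** Under Statistical analysis, verum acupuncture is compared with standard medical care. The terms are treatment group, patients' expectations "and their respective baseline values (linear covariates) using a univariate analysis of covariance".

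**Sham comparison.** If the first test is significant, "a second univariate analysis of covariance on the primary outcome will be conducted as a function of the treatment group", now verum against sham, with the same two covariates.

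**Secondary outcomes.** "The same covariance models will be applied for secondary outcome measures", reported descriptively.

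No other section adds age or chemotherapy type to a model. Both are recorded at baseline (Data collection).

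**Sample size.** The abstract gives 75 patients in total, "pending an alpha of 0.05, a power of 0.8, and an estimated effect size of 0.80". The Sample size calculation section bases 25 per group on a two-sided t "test between independent groups (verum acupuncture versus standard medical care) with an α of 0.05".

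**The concern.** Blocked allocation within strata keeps the arms alike on the stratification factors. If those factors are prognostic, the treatment estimate then varies less from trial to trial than under simple randomisation. An ANCOVA without the factors does not see this. It leaves their variance in the residual and reports a standard error for a less precise design than the one used.

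The protocol's reason for stratifying is that both variables matter for the course of the symptom, so leaving them out sits badly with its own rationale. The article also lists the covariates for both primary models and extends the list to the secondary outcomes. This is therefore a choice that the document makes, not detail left to a later plan.

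What is at stake is precision. With 25 patients per arm, intervals may be wider than the design warrants. Because the sham comparison is tested only after a significant first step, a conservative first step also makes it less likely that the patient-blinded comparison is reached.

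**Working it through.** **1. The plan's own figure.** Inputs from Sample size calculation: d = 0.8, two-sided α = 0.05, power 0.80.

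- Normal approximation: n = 2 × (1.960 + 0.842)² / 0.8² = 2 × 7.85 / 0.64 = 24.5, so 25 per group.
- Exact noncentral t: power is 0.791 at n = 25 and 0.807 at n = 26.

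The stated 25 is reproduced within tolerance. The calculation uses an unadjusted t test and counts on no gain from strata or covariates.

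**2. Expected size of the effect.** Let R² be the share of the residual variance, after baseline and expectation, that the two factors explain. With near-perfect balance:

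- planned SE / SE with the factors ≈ 1/√(1 − R²);
- true type I error of the planned test ≈ P(|Z| > 1.96/√(1 − R²)).

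For R² = 0.05/0.10/0.20/0.30 the SE ratio is 1.026/1.054/1.118/1.195. The critical values become 2.01/2.07/2.19/2.34, which give a type I error of 4.4/3.9/2.8/1.9%.

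**3. Simulation.** From the protocol: 75 patients, three arms, 1:1:1, stratified blocks, d = 0.8, two-sided 5%. Assumed, because the protocol is silent: four equally likely strata (2 × 2), blocks of 3 or 6, a range of R², and factors unrelated to baseline and expectation. There were 10,000 trials per setting. Residual SD after baseline and expectation was set to 1. The planned model is compared with the same model plus the two factors (planned / with factors).

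| R² | CI width ratio | Type I error, % | Coverage, % | Power at d = 0.8, % |
|---|---|---|---|---|
| 0 | 0.997 | 5.3 / 5.3 | 95.1 / 95.1 | 78.1 / 77.9 |
| 0.05 | 1.023 | 4.4 / 4.9 | 95.5 / 95.0 | 77.7 / 79.3 |
| 0.10 | 1.052 | 3.8 / 5.0 | 96.1 / 94.9 | 78.0 / 81.2 |
| 0.20 | 1.118 | 3.1 / 5.2 | 96.7 / 94.8 | 79.5 / 85.5 |
| 0.30 | 1.198 | 2.1 / 5.0 | 98.0 / 94.9 | 80.1 / 89.5 |

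The width ratios agree with step 2. Power differences are −0.2, 1.6, 3.1, 6.0 and 9.4 points.

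**4. Sensitivity of the power figure.** Step 3 measures d against the residual SD. If d = 0.8 is measured against the outcome SD and baseline correlates 0.5 with outcome, the residual variance is 1 − 0.5² = 0.75. The effective difference is then 0.8/√0.75 = 0.92 residual SDs. Planned power is already close to 90%, and the gap shrinks to about 0/1/2/3/6 points at R² = 0/5/10/20/30%, with simulation error of up to about a point. SE inflation and type I error are essentially unchanged.

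**5. If baseline already carries the factors.** Suppose the factors shift baseline and outcome equally and explain 10/20/30% of *total* outcome variance (correlation 0.5; 5,000 runs per setting). The planned SE is then only about 2/4/8% too large. Power at d = 0.8 is 0.88/0.89/0.88 as planned, against 0.89/0.91/0.92 with the factors.

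**The case against.** **The loss is conditional.** The protocol says that the factors affect the course of dysgeusia but gives no size. What counts is what they explain after baseline and expectation. Baseline is rated after patients have already had chemotherapy and developed the symptom, so it may absorb part of any age or regimen effect. This stands: at R² = 0 nothing is lost, and the range must start there.

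**No promised power is lost.** A reader might infer that the trial is underpowered because of the omission. The documents do not support that. The 25 per group come from an unadjusted t test, and the planned model delivers about what that test promises (78 to 80% in step 3, against 79.1%) or more. What is given up is a gain that the design makes available.

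**Validity is intact.** A reader might also infer that a true level below 5% and coverage above 95% invalidate the tests. They do not: the deviation is only in the conservative direction, and the estimate is unbiased.

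**Neighbouring choices are not errors.** Separate two-arm ANCOVAs in a fixed order are valid. A pooled three-arm model is a preference that assumes a common residual variance and common covariate slopes across needling and dietary-advice arms. The variables in the imputation model are detail that an article commonly leaves to the full plan. Neither belongs to this point.

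**Conclusion.** The point holds as one of efficiency, not validity. The omission is explicit and certain; its size is not. Over an assumed residual R² of 0 to 30%, the planned standard error is between 0 and about 20% too large, and the true type I error lies between about 5% and 2%. Power forgone at d = 0.8 runs from none to about 6 points with a baseline-outcome correlation of 0.5, or about 9 points when d is measured in residual SDs. The lower part of these ranges is the more relevant if baseline phantogeusia already reflects age and regimen.

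These figures rest on assumed strata, block lengths and covariate effects, none of which the protocol states. The case for changing the plan does not depend on the exact value. Adjustment costs almost nothing if the factors are uninformative, and it restores nominal coverage if they are as prognostic as the reason for stratifying implies.

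**What to change.** Add age (continuous, or in the categories used for stratification) and type of chemotherapy (as stratified) to baseline value and expectation in both primary ANCOVAs and in the secondary-outcome models. Record the change before unblinding. The article reports that recruitment is continuing and that no interim analysis is planned, so on its own account there was still time.

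The cost is one sentence and a few degrees of freedom, depending on the number of levels. A two-arm model on 50 patients with intercept, group, baseline and expectation leaves 50 − 4 = 46 residual degrees of freedom; two two-level factors would leave 44. With uninformative factors, that costs about 0.2 power points in the simulation (78.1 against 77.9%). No new data are needed.

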# Hypoglossal acupuncture for acute chemotherapy-induced dysgeusia in patients with breast cancer: study protocol of a randomized, sham-controlled trial

**DOI:** 10.1186/s13063-019-3525-y

**Published:** 2019-07-04

**Keywords:** Acupuncture, Cancer, Chemotherapy, Dysgeusia, Taste disorders, Randomized controlled trial

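### The plan makes the verum-versus-sham analysis of the primary outcome itself, not only its confirmatory status, depend on a significant result against standard medical care

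*Protocol article*

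**What the plan says.** The Statistical analysis section of the protocol article sets a fixed order. Verum acupuncture is compared with usual care first, "which in case of significant effects will be followed by the comparison of acupuncture vs. sham acupuncture". The condition is then repeated for the model: "If the analysis reveals a statistically significant between-group difference, a second univariate analysis of covariance on the primary outcome will be conducted". The verum-sham difference and its 95% confidence interval are described only as output of this second model. Both steps use a two-sided alpha of 5%, on the ground that "Because of hierarchical testing of the hypotheses, no alpha level adjustment is necessary".

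The Sample size calculation section powers the first step only: "a sample size of *n* = 25 patients per group was considered sufficient to detect an effect of *d* = 0.8", for "verum acupuncture versus standard medical care) with an α of 0.05 and a power of 1 − β = 0.8".

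The title describes the article as a "study protocol of a randomized, sham-controlled trial", and the Objectives section gives efficacy and safety as the aim. Under Blinding, "patients of the two acupuncture groups will be blinded to whether they receive verum or sham acupuncture"; patients given dietary advice are not blinded. The outcome assessors and the statistician are blinded in all arms. The primary outcome is phantogeusia at T2, rated on an 11-point NRS.

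**The concern.** In a fixed-sequence procedure the second hypothesis may be tested at full alpha because no confirmatory claim is made on it unless the first is rejected. That requires the claim to be conditional. It does not require the estimate to be withheld, and withholding it gains no error control.

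The estimate at risk is an important one. Phantogeusia is the patient's own sensation, so blinding the staff who hand out questionnaires does not remove expectation effects from the comparison with dietary advice. Only the sham comparison has blinded patients, and the Discussion says that a sham control serves to account for expectation, conditioning and attention. A non-significant first step is also no evidence about verum versus sham. It could arise by chance, or because dietary advice helps; the Background says dietary counseling has the best evidence available so far. In either case a reader would want the verum-sham estimate for the primary outcome, and the plan as written does not produce it.

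**Working it through.** **Inputs.** From the protocol article: 25 per arm, d = 0.8, two-sided alpha 0.05, power 0.8 (Sample size calculation); three arms in ratio 1:1:1 (Study design); the condition on the second model (Statistical analysis). Assumed here, because the article gives no figure: true effects other than 0.8, and the correlation of the ANCOVA covariates with the outcome. The article says that no previous effect sizes were available.

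**1. The plan's own figure.** By the normal approximation, n per arm = 2(1.96 + 0.8416)² / 0.8² = 24.5, so 25, with power 0.807 at n = 25. With the exact t test, n = 25.5, so 26, and power at n = 25 is 0.791. The stated 25 per group reproduces within rounding.

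**2. Chance that the sham model is not run, unadjusted t test.** This chance is 1 minus the power of the first step. The noncentrality is d√(25/2), with 48 degrees of freedom and critical value 2.011.

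| True verum-versus-care effect | Noncentrality | Power | Sham model not run |
|---|---|---|---|
| 0.8 (planned) | 2.828 | 0.791 | 0.21 |
| 0.6 (assumed) | 2.121 | 0.547 | 0.45 |
| 0.5 (assumed) | 1.768 | 0.410 | 0.59 |

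**3. The same with covariate adjustment.** If the covariates together correlate r with the outcome, the residual SD shrinks by √(1 − r²) and the effective effect is d/√(1 − r²).

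| True effect | r (assumed) | Effective effect | Sham model not run |
|---|---|---|---|
| 0.8 | 0.3 | 0.8/0.954 = 0.839 | 0.17 |
| 0.8 | 0.6 | 0.8/0.8 = 1.000 | 0.07 |
| 0.5 | 0.3 | 0.5/0.954 = 0.524 | 0.56 |
| 0.5 | 0.6 | 0.5/0.8 = 0.625 | 0.42 |

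Using 46 instead of 48 degrees of freedom, to allow for two covariates, changes none of these by more than 0.001.

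**4. A side effect of showing the estimate only after a significant first step.** Both comparisons share the verum arm, so trials that pass the first step tend to have a favourable verum mean. In a simulation of three normal arms of 25 (50,000 runs, no covariates) with both true effects at 0.5, the verum-sham estimate averaged 0.63 among trials that passed. With a true care effect of 0.5 and a true sham effect of 0, it averaged 0.13. Over all trials the averages were 0.50 and 0.00.

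**5. After the fix.** If the model is always run, the chance of having no verum-sham estimate for the primary outcome falls to 0, and the selection in step 4 disappears. The familywise error rate stays at 0.05, because the confirmatory claim remains conditional.

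**The case against.** The strongest reply is that nothing is wrong with the inference. The order is prespecified, it matches the comparison that was powered, and alpha is controlled. The wording may be no more than shorthand for conditional testing, since it is introduced as an order of tests. Nothing forbids a descriptive estimate afterwards, and a separate analysis plan could provide for one. T2 data are collected in every arm, so the estimate remains computable.

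Much of this stands. The order is a legitimate design choice and is not disputed here. The shorthand reading does not settle the matter, however: the article states a rule for when the second model is conducted, states the condition twice, and gives no alternative for the primary outcome. That is a stated rule, not a detail left out for brevity. An estimate added after a failed first step could still be computed, but it would be post hoc.

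A reader might also infer that the trial could end with no patient-blinded comparison at all, so that the sham arm contributes nothing. The article does not support that. It applies the same covariance models to the secondary outcomes and reports them descriptively. Those outcomes include phantogeusia from the daily log. The Kaplan-Meier analysis of time to symptom relief carries no stated condition. The text does not say whether the condition extends to these analyses, so only the T2 primary-outcome estimate is clearly at risk.

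Nor is it a defect that the article does not spell out what a significant first step alone would support. That is interpretive detail, and if the first step is significant the sham result is produced alongside it.

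**Conclusion.** The point holds for the primary outcome. Followed as written, a non-significant comparison with standard medical care leaves no planned verum-sham difference or 95% confidence interval for T2 phantogeusia.

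Under the plan's own d = 0.8 the chance is about 21% unadjusted, which is essentially the type II error the design accepts. It is about 7 to 17% for covariate correlations of 0.6 to 0.3. At d = 0.5 it is about 59% unadjusted and 42 to 56% adjusted. The smaller effect and the correlations are assumptions.

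Severity is moderate. The primary test is not biased and error control is intact, but a sham-controlled efficacy trial should not make its patient-blinded primary estimate depend on the outcome of another comparison.

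**What to change.** Replace the condition on conducting the second model with two sentences to this effect:

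- The verum-versus-sham ANCOVA on T2 phantogeusia is run, and its adjusted difference and 95% confidence interval are reported, whatever the result against standard medical care.
- Its p value is confirmatory only if the first comparison is significant; otherwise it is descriptive.

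The cost is those two sentences. The testing order, alpha control, sample size and data collection stay as they are. The article reports the trial as still recruiting with no interim analysis planned, so the change should be made and dated before any results by group are known.
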